**Project title**
(Un)treated cervical intraepithelial neoplasia (CIN) and adverse obstetrical and perinatal outcomes.

**Background**

Cervical cancer screening has been in place in the Netherlands for several decades. Aim of the screening program is to identify and treat premalignant cervical lesions before they progress to cancer. This has led to a strong reduction in cervical cancer incidence and mortality. However, the downside of this screening is unnecessary referral of many women without any abnormalities or lesions that only have very low risk of progressing to cancer. This downside is even more pronounced in the new screening program where high-risk human papillomavirus (hrHPV) testing has replaced primary cytology testing. Most high-risk cervical lesions but inevitably also many lesions with a lower risk are treated by large loop excision of the transformation zone (LLETZ). Various studies and meta-analyses point to an increased risk of perinatal complications such as preterm delivery, low birth weight, premature rupture of membranes and caesarean delivery after LLETZ treatment. Therefore, overtreatment of fertile women has main priority for policymakers. However, it is unknown whether this increased risk is only due to the excision procedure itself, to the underlying cervical intraepithelial neoplasia (CIN) or to secondary risk factors which are associated with both preterm birth and CIN. The purpose of this study is to investigate the association between untreated CIN, treated CIN and adverse obstetrical and perinatal outcomes.

**Research question**

What is the association between women with (un)treated CIN and risk of adverse obstetrical and perinatal outcomes?

**Hypothesis**
Women with a history of CIN, and especially women who have been treated for CIN, are at increased risk of premature birth. The depth of treatment and number of treatments will increase the risk of premature birth.

**Methods**

To answer the research question we started to explore the possibilities of linking treatment data of CIN from the Dutch pathology database (PALGA) with the Dutch perinatal database (Perined). For this purpose involvement of a trusted third party (ZorgTTP) and Statistics Netherlands (CBS) is considered necessary for linking PALGA data to perinatal outcome data from Perined. A mandatory condition is that personal identifiers of the mother are available and that pseudonyms of PALGA and Perined can be harmonized. Furthermore the procedure must meet all current privacy legislation issues.
A specially designed ‘Privacy Verzend Module’ (PVM) delivered by ZorgTTP will be used to convert ZorgTTP pseudonyms (based on social security number (BSN)) into CBS BSN-pseudonyms and to send them to CBS. At CBS the BSN-pseudonyms will be linked and the corresponding BSN will be assigned. Based on the secondary keys (such as date of birth, postal code and sex) the linking results will be checked. When identical the variable ‘Rinpersoon’ is added to the dataset. Based on ‘Rinpersoon’ the PALGA data are linked to the Perined data (Rinpersoon_mother).
After linkage of the PALGA and Perined data at CBS, the researchers will analyze only anonymized data within the CBS ICT environment.

**PALGA selection**Three groups will be selected in PALGA.

Group 1) Women with untreated CIN
Inclusion criteria:
 - Period: 01-01-2005 until 31-12-2015
 - Age: 29-41 years at date of CIN diagnosis (so women invited for three screening rounds are
 included: age 30, 35 and 40)
 - Histologic diagnosis: CIN1, CIN2, CIN3 or AIS diagnosed via biopsy
 Exclusion criteria: histology through treatment, such as LLETZ, ablation, hysterectomy or other.
Group 2) Women with treated CIN
Inclusion criteria:
 - Period: 01-01-2005 until 31-12-2015
 - Age: 29-41 years at date of CIN diagnosis (so women invited for three screening rounds are
 included: age 30, 35 and 40)
 - Histologic diagnosis: CIN1, CIN2, CIN3 or AIS diagnosed via biopsy or treatment
 - Requirement: at least one treatment outcome through LLETZ
Group 3) Control group: women without CIN
Inclusion criteria:
 - Period: 01-01-2005 until 31-12-2015
 - Cytologic diagnosis: normal cytology
Exclusion criteria:
 - Cytologic diagnosis: ASCUS or more in history or follow-up
 - Histologic diagnosis: CIN1 or more in history or follow-up
Group 3 will be matched (1:3?) with group 1 and 2 based on age at and year of diagnosis and urbanization.

Variables

- Age of women during cytology/biopsy/treatment
- Date of cytology/biopsy/treatment
- Number of biopsies/treatments
- Histologic diagnosis
- Macroscopic description to calculate the size/volume of the biopsy/treatment by a datamining
 procedure.
- Type of treatment cannot be further specified

**Perined selection**- Period: 01-01-2010 until 31-12-2018
- Pregnancies between 16-24 weeks could be in the database, but this is not required
- Pregnancies of 24 weeks and more are mandatory in the database

Maternal variables
- Conception (spontaneous or with medical help)
- General history
- Obstetrical history
- Gravidity
- Parity
- Singleton or multiple pregnancy (twins, triplets etc)
- Gestation in days and weeks
- Age of the mother at childbirth (calculation through date of childbirth and age at histology date?)
- Date of childbirth
- Start of delivery (spontaneous, iatrogenic)
- Way of delivery (spontaneous, assisted vaginal delivery, caesarean section)
- Presenting part during delivery
- Problems during current pregnancy

Neonatal variables
- Birth weight in grams
- Apgar score after 5 minutes
- Congenital diseases
- Admission after birth (high care, intensive care, post-ICHC; period of admission in days)
- Perinatal death (gestation, antepartum/durante partu/postpartum)

Risk factors for preterm birth
- Ethnicity
- Smoking
- Immunosuppressive medication
- BMI
- General history: infectious diseases, auto-immune diseases, organ-transplantation, diabetes
 mellitus, epilepsy, psychiatric diseases, thyroid disorders
- Obstetrical history: curettage in history, history of abortion, history of preterm birth
- Short interval between pregnancies
- Conception through IVF/ICSI/egg donation
- Multiple pregnancy (twins, triplets etc)
- Nulliparous women
- Problems during current pregnancy: maternal infection, pre-eclampsia, gestational diabetes,
 placental problems
- Congenital diseases

Date of histology and date of childbirth will be used to make a selection of women who were treated before and after their pregnancy to additionally compare perinatal outcomes before treatment and after treatment.

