**Parties involved**

Radboudumc, Erasmusmc, BBMRI, Perined, PALGA, ZorgTTP, CBS

**Changes in the plan:**During data-preparation
- We decided to exclude all multiple pregnancies (twins, triplets etc)
**-** We decided to include women with only treatment after the pregnancy, but biopsy-proved CIN before the pregnancy in group 1 (untreated CIN)
- We decided to only use the spontaneous births for our analysis
- We could not adjust for all potential confounders, as not all these data was (well) documented in Perined, such as smoking, BMI, immunosuppressive drug use, sexual behavior and socio-economic status
- We could only calculate the size of the excised volume for a select group of women, as the macroscopic description was not always (in three dimensions) identifiable. We could, therefore, not use this variable in the main multivariate analysis.
During data-analysis
- The two selected groups from PALGA were matched with a control group, but after linking this data with Perined and looking per pregnancy instead of per women the groups were not completely equal anymore based on these matching criteria. We therefore decided, for example, to also include ‘urbanization’ in the multivariate analysis.

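### The only pathology end date stated is 31-12-2015 but births run to 31-12-2018; if treatment retrieval stopped there, some late pregnancies are wrongly counted as untreated CIN

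*Protocol*

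**What the plan says.** Under PALGA selection in Methods, each of the three groups has the same first inclusion criterion: "Period: 01-01-2005 until 31-12-2015". No other pathology period appears in the protocol. The Perined selection in the same section uses "Period: 01-01-2010 until 31-12-2018".

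The treatment criteria carry no dates of their own. Group 1 has "Exclusion criteria: histology through treatment, such as LLETZ, ablation, hysterectomy or other". Group 2 has "Requirement: at least one treatment outcome through LLETZ". Only group 3 mentions records beyond entry, through the exclusion "Histologic diagnosis: CIN1 or more in history or follow-up", and no end date is given for that follow-up.

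Exposure depends on the order of dates. Methods states that "Date of histology and date of childbirth will be used to make a selection of women who were treated before and after their pregnancy", to compare outcomes before and after treatment. The list of changes in the plan adds the decision to "include women with only treatment after the pregnancy, but biopsy-proved CIN before the pregnancy in group 1", and says that the data were examined per pregnancy. The number of treatments is a planned sub-analysis (Analyses) and part of the hypothesis.

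**The concern.** To classify a 2017 birth as following treated or untreated CIN, one must know every excision up to that pregnancy. The only stated pathology window closes before it. Taken literally, a woman with a CIN biopsy in 2015, a LLETZ in 2016 and a birth in 2017 enters the untreated group. For a woman already in group 2, a second LLETZ in 2016-2018 before a birth is missing from her treatment count.

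The Background asks whether the excess risk comes from the excision, the underlying lesion or shared risk factors. Treated versus untreated CIN is the contrast that bears on the first two. If treatment raises risk, as the Hypothesis expects, treated pregnancies hidden in group 1 raise its preterm risk and part of an excision effect is credited to the lesion. Any gradient with number of treatments is likewise measured on incomplete counts.

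**Working it through.** The protocol gives no event rate, effect size or sample size, so it has no figure to reproduce. The check is date arithmetic followed by a mixture calculation on assumed inputs.

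**1. Dates (from the protocol).** 01-01-2010 to 31-12-2018 is 3287 days. 01-01-2016 to 31-12-2018 is 1096 days. 1096 / 3287 = 33.3% of the birth window lies after the last stated pathology date.

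**2. Who is affected.** Only group 1 pregnancies with a first excision after 31-12-2015 and before the pregnancy are moved to the wrong group. Women already excised by 2015 stay correctly in group 2. Excision only after the pregnancy counts as untreated under the amended rule.

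**3. Size, by simulation.** All of these inputs are assumptions:
- biopsies spread evenly over 2005-2015;
- exponential time from biopsy to conception, mean 3 years;
- birth 0.75 years after conception, kept if in 2010-2018;
- 40% to 70% of biopsied women excised, after an exponential delay with mean 3 to 6 months;
- 1% to 3% per year excised among the rest;
- excisions dated 2016 or later not seen.

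Results, with 4 million women per scenario:
- about 20% of births classed as untreated are conceived after 2015;
- 5.3% to 21.9% of those follow an unseen excision;
- this is 1.1% to 4.3% of all births classed as untreated.

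**4. Effect on the odds ratio.** Assume true preterm risks of 10% (treated) and 6% (untreated). With a share f of group 1 actually treated:

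observed group 1 risk = 0.06 + 0.04 × f

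observed odds ratio = (0.10/0.90) / [risk / (1 − risk)]

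| Births | f | Group 1 risk | Odds ratio |
|---|---|---|---|
| No contamination | 0 | 6.00% | 1.74 |
| All, low | 1.1% | 6.04% | 1.73 |
| All, high | 4.3% | 6.17% | 1.69 |
| Conceived from 2016, low | 5.3% | 6.21% | 1.68 |
| Conceived from 2016, high | 21.9% | 6.88% | 1.50 |

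**5. Cross-check without the simulation.** Let m be the assumed share of 2016-2018 group 1 births with an unseen prior excision. With births spread evenly, f = m × 1096/3287. Take an untreated risk of 6% and a true odds ratio of 2.0.

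| m | All births | 2016-2018 births only |
|---|---|---|
| 5% | 1.97 | 1.91 |
| 10% | 1.94 | 1.83 |
| 20% | 1.88 | 1.68 |
| 30% | 1.83 | 1.55 |

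For a true odds ratio of 1.5, the overall values at the same m are 1.49, 1.48, 1.45 and 1.43. Untreated risks of 4% or 8% barely change these results. Both methods agree on direction and order of size.

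**6. Untreated versus control.** Contamination of group 1 pushes this odds ratio up. If retrieval stopped in 2015, women whose CIN or excision was first recorded later would remain among the controls, which pushes it down. The protocol gives nothing from which to weigh one against the other.

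**The case against.** The strongest reply is that the period is an eligibility window, not a limit on data retrieval. It stands among the inclusion criteria beside age at diagnosis. The group 1 treatment exclusion is undated. Group 3 has the same period, yet its history and follow-up are searched, so the period need not bound the records consulted. Treatment dates and counts are listed as variables without a cut-off. Births running some years past the qualifying diagnosis is ordinary cohort design, and extraction details may sit in a document not shown.

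Much of this stands. A reader might infer that excisions in 2016-2018 definitely went unseen and that the reported odds ratio is diluted. The protocol does not support that: it says neither that later histology was retrieved nor that it was not. What remains is that the follow-up wording is given for group 3 alone, and that nothing in groups 1 and 2 assures treatment data up to each birth, which the date-order rule requires.

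Two further points also stand. The overall shift is small, and the larger figures concern late conceptions, for which no separate analysis is planned. The lists of changes also show that linkage, analysis and peer review have already taken place, so a fresh extract would not be a trivial request.

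**Conclusion.** The point holds conditionally. The end of treatment ascertainment is not stated for groups 1 and 2, and the only pathology date given is three years short of the last births. If retrieval stopped there, the treated-versus-untreated odds ratio is biased toward 1, provided treatment does raise risk as hypothesised, and the number of treatments is undercounted.

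The overall bias is modest, from 1.74 to between 1.69 and 1.73, and it is concentrated in conceptions from 2016 (1.50 to 1.68). Those figures rest entirely on assumed biopsy timing, excision rates and preterm risks. The flattening of the treatment-count gradient was not quantified.

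Two stronger readings should be avoided. One is that a third of the data is compromised: 33.3% is a share of calendar time, and only a small part of those births would be misclassified. The other is that untreated versus control is necessarily inflated: missed events among controls act in the opposite direction, so the net shift is uncertain. The matter should be addressed because the possible bias falls on the study's central contrast and can be checked with data already held.

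**What to change.** Keep 2005-2015 as the window for the qualifying diagnosis. State the date to which cervical histology, including treatment specimens, was retrieved for all three groups. Classify each pregnancy, and count treatments, from all excisions dated before conception, using histology through 31-12-2018.

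Where that histology is not held, repeat the primary three-group comparison and the number-of-treatments analysis on births conceived on or before 31-12-2015. Report these beside the main results and state that exposure for later births is incompletely observed.

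If later histology was already retrieved, the cost is a sentence of clarification. The restricted analysis needs no new data but gives up some precision, roughly a fifth of group 1 births under the assumptions above. A new PALGA extract costs more, since it would have to go again through the pseudonym conversion and linkage described in Methods.

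### The treated group requires an LLETZ in 2005-2015 but not before the pregnancy, and the later re-grouping repairs this only in part; it is also unstated whether treatment records reach the 2016-2018 births

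*Protocol*

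**What the plan says.** Under Methods, PALGA selection, the untreated and treated CIN groups share the line "Period: 01-01-2005 until 31-12-2015".

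- **Treated group (group 2).** CIN may be diagnosed by biopsy or at treatment. The treatment criterion is "Requirement: at least one treatment outcome through LLETZ". It is not tied to the date of any pregnancy.
- **Untreated group (group 1).** The exclusion is "Exclusion criteria: histology through treatment, such as LLETZ, ablation, hysterectomy or other", with no end date.
- **Controls (group 3).** One exclusion is "Histologic diagnosis: CIN1 or more in history or follow-up". The control exclusions are the only ones that mention follow-up, and they give no end date.

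Under Perined selection, births are taken from a different window: "Period: 01-01-2010 until 31-12-2018". The same section says: "Date of histology and date of childbirth will be used to make a selection of women who were treated before and after their pregnancy". That selection serves an additional comparison and does not define the main groups. The variable list includes "Date of cytology/biopsy/treatment", date of childbirth and gestation, so the order of events can be reconstructed.

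Under Changes in the plan, one decision made during data preparation reads: "We decided to include women with only treatment after the pregnancy, but biopsy-proved CIN before the pregnancy in group 1 (untreated CIN"). The same section says that after linkage the data were examined by pregnancy. The primary outcome is the odds ratio of preterm birth between the three groups, with a sub-analysis by number of biopsies or treatments.

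**The concern.** The Background asks whether the excess risk comes from the excision, from the underlying CIN, or from shared risk factors. The treated versus untreated contrast addresses this, and it needs to be known for each pregnancy whether an LLETZ had already taken place.

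Two features of the stated design can break that.

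1. A pregnancy that ended before the LLETZ can meet the treated criteria. It carries no effect of excision and dilutes the treated group.
2. If treatment records stop with the pathology window, a pregnancy that followed an LLETZ in 2016-2018 stays in the untreated group and raises its risk.

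If LLETZ increases risk, both errors shrink treated versus untreated, and the second also inflates untreated versus control. The Hypothesis further expects risk to rise with number of treatments. A count that includes procedures after the birth would blur that gradient.

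**Working it through.** The protocol gives no event rates, sample size or group sizes, so there is no figure of its own to reproduce. The check has three parts.

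**1. The windows**
- Pathology window: 2005-2015, 11 years. Birth window: 2010-2018, 9 years. Overlap: 2010-2015, 6 years.
- A birth before the LLETZ is therefore possible by design. If LLETZ and birth dates were independent and uniform (an assumption), the share of pairs with the birth first would be 6² / (2 × 11 × 9) = 36/198 = 18.2%. This is before the re-grouping under Changes in the plan, which removes an unknown part of it.
- Births in 2016-2018 cover 3 of 9 years. Not all of these could follow an unseen LLETZ: for a term birth conceived after 31-12-2015, delivery falls from about autumn 2016. That leaves about 27 of 108 months, or 25%.

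**2. What the re-grouping covers**

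| Order of events | Group under the stated rules |
|---|---|
| LLETZ, then pregnancy | Treated |
| Biopsy-proven CIN, pregnancy, then first LLETZ | Untreated, by the later change |
| Pregnancy, then CIN diagnosis and LLETZ | Still meets the treated criteria; no rule removes it |
| Pregnancy, then CIN first found at the LLETZ | As above; there is no earlier biopsy for the change to act on |
| One woman with births before and after LLETZ | No per-pregnancy rule; the change is worded by woman |
| Pregnancy, then biopsy, never treated | Meets the untreated criteria, although CIN was not yet diagnosed |

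**3. Illustrative size**

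Assumed: true risk ratio 1.8 for treated and 1.0 for untreated, both against control. The misclassified shares of 10-30% are also assumed.

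*First error* (share f of treated pregnancies precede LLETZ): observed ratio = f × 1.0 + (1 − f) × 1.8.
- f = 0.10: 0.10 + 1.62 = 1.72
- f = 0.30: 0.30 + 1.26 = 1.56

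*Second error* (a quarter of untreated births at risk, share q of these after an unseen LLETZ): untreated versus control U = 1 + (q/4) × 0.8; treated versus untreated = 1.8/U.
- q = 0.10: U = 1.02; 1.8/1.02 = 1.76
- q = 0.30: U = 1.06; 1.8/1.06 = 1.70

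*Both together:* 1.72/1.02 = 1.69, down to 1.56/1.06 = 1.47.

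*On the odds ratio scale*, with assumed preterm risks of 5% (control), 6% (untreated) and 9% (treated), the true treated versus untreated odds ratio is 1.55.
- With 5-18.2% of treated pregnancies really untreated, it is 1.52-1.45.
- With 5-10% of all untreated pregnancies really treated, it is 1.51-1.47, and untreated versus control rises from 1.21 to 1.25-1.28.
- With both, it is 1.48-1.37.

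**The case against.** The strongest reply is that the protocol already handles timing. The data were examined by pregnancy, and women treated only after the pregnancy go to the untreated group if CIN was proven beforehand. This stands in part. A reader might infer that treatment status is fixed per woman throughout; the Changes in the plan section does not support that. What survives is narrower: the births in the table that the change does not reach.

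A second reply is that the period line may define only the window for the qualifying diagnosis, with treatment records running later. The untreated exclusion has no end date, and the control exclusions speak of follow-up. This also stands. A reader might infer that LLETZ in 2016-2018 certainly goes unseen, but the text supports only a conditional statement.

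A third reply is that silence is not a rule. The protocol does not say that procedures after the birth are counted; it gives no cut-off, and a statistical analysis plan that is not shown may supply one. That is fair for the counting rule. It does not answer the point on group membership, because the protocol itself fixes the treated criteria, both windows and a partial re-grouping. Applied as written, these put some pre-LLETZ births in the treated group.

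Finally, the shares and the ratio of 1.8 are assumed, and the Hypothesis expects CIN itself to carry some risk. This stands: a higher untreated risk makes the dilution smaller. With an untreated ratio of 1.2, the true contrast is 1.8/1.2 = 1.50, and f = 0.30 gives (0.36 + 1.26)/1.2 = 1.35. That is a 10% reduction, against 13% (1.56/1.80) when the untreated ratio is 1.0.

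**Conclusion.** The point holds in a limited form. The stated criteria allow pregnancies before both CIN diagnosis and LLETZ to count as treated, give no per-pregnancy rule for women with births on both sides of the LLETZ, and set no cut-off for counting treatments. Whether LLETZ in 2016-2018 is missed depends on the reach of the treatment records, which the protocol leaves open.

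If LLETZ raises risk, the direction is clear: treated versus untreated is attenuated, and under the second error untreated versus control is also inflated. The size cannot be obtained from the protocol, and the figures above rest entirely on assumed risks and shares.

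A reader might infer that the study's conclusion moves from excision to underlying CIN. The documents do not support that: in every illustrated case treated versus untreated stays above 1, and the second error on the risk ratio scale lifts untreated versus control only to 1.02-1.06. This is avoidable bias in the primary contrast and worth correcting, but it does not by itself overturn the study.

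**What to change.** Assign exposure for each pregnancy from CIN and treatment records dated before it, with conception taken as date of childbirth minus gestation.

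- **Treated:** LLETZ before conception.
- **Untreated CIN:** biopsy-proven CIN before conception and no excision before delivery.
- **Excision between conception and delivery:** excluded.
- **Pregnancy before any CIN diagnosis:** removed from groups 1 and 2 and kept for the before/after comparison.
- **Number of treatments:** count only procedures before conception.

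State the date to which treatment records run for groups 1 and 2. If it is 31-12-2015, restrict births to those conceived by that date, as the main or a sensitivity analysis, or extend the extract where feasible.

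The re-grouping is recoding with dates already listed as variables, followed by a re-run. The restriction costs some late births. Extending the extract costs more, because it would have to pass again through the trusted third party and Statistics Netherlands. Since the protocol already records changes made after peer review, the recoded classification and the restriction are the practical first steps.
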